#### 11.4 Expectedness, Pre-Existing Conditions, and Persistent Adverse Events

- ***Expectedness:*** The study Sponsor will be responsible for determining whether an AE is expected or unexpected. An AE will be considered unexpected if the nature, severity, or frequency of the event is not consistent with the risk information previously described for the investigational product.
- ***Pre-Existing Conditions:*** If a pre-existing condition worsens in severity, the worsening may require reporting as an AE or SAE. In addition, if a condition present at baseline resolves and then recurs, the reoccurrence may require reporting as an AE or SAE.
- ***Persistent Adverse Events:*** A persistent AE is one that extends continuously, without resolution (is ongoing). A persistent AE is reported only once unless the grade and/or frequency become more severe. If the grade becomes more severe the original AE will be considered to have stopped on the date the severity increased and the AE must be reported again with the higher grade and/or frequency.

## 11.5 Cytokine Release Syndrome Grading

| Grade          | Description of Symptoms                                                                                                                                                                                                                                                              |
|----------------------------|--------------------------------------------------------------------------------------------------------------------------------------------------------------------------------------------------------------------------------------------------------------------------------------|
| 1: Mild             | Not life-threatening, require only symptomatic treatment such as antipyretics and anti-emetics (e.g., fever  $\geq 38.0^{\circ}\text{C}$ , nausea, emesis, fatigue, headache, myalgia, malaise)                                                                          |
| 2: Moderate         | Require and respond to moderate intervention: 
 
• Oxygen requirement for low flow nasal cannula or blow by oxygen, or
 
• Hypotension responsive to fluids
 
                                                        |
| 3: Severe           | Require and respond to aggressive intervention: 
 
• Oxygen requirement for high flow nasal cannula, face mask, non-rebreather or Venturi mask, and/or
 
• Hypotension requiring a one vasopressor with or without vasopressin
 
 |
| 4: Life threatening | Life-threatening: 
 
• Requirement for positive pressure support including ventilator support, CPAP or BiPAP
 
• Hypotension requiring multiple vasopressors (excluding vasopressin)
 
                                           |
| 5: Fatal            | Death                                                                                                                                                                                                                                                                                |

1: Fever is defined as temperature  $\geq 38.0^{\circ}\text{C}$  not attributable to any other cause. In patients who have CRS then receive antipyretics or anti-cytokine therapy such as tocilizumab or corticosteroids, fever is no longer required to grade subsequent CRS severity. In this case, CRS grading is driven by hypotension and/or hypoxia.

2: CRS grade is determined by the more severe event: hypotension or hypoxia not attributable to any other cause. For example, a patient with temperature of  $39.5^{\circ}\text{C}$ , hypotension requiring one vasopressor and hypoxia requiring low-flow nasal cannula is classified as having Grade 3 CRS. Organ toxicities associated with CRS may be graded according to CTCAE v5.0 but they do not influence CRS grading.

3: Low-flow nasal cannula is defined as oxygen delivered at  $\leq 6$  liters/minute. Low flow also includes blow-by oxygen delivery, sometimes used in pediatrics. High-flow nasal cannula is defined as oxygen delivered at  $> 6$  liters/minute

## 11.6 Neurologic Toxicity Grading

Individual neurologic symptoms should be graded using CTCAE v5, however cumulative neurologic toxicity will be graded according to the Neurologic Toxicity Grading System, see Section 14, Appendix 4 – Neurologic Toxicity Grading System.

## 11.7 Serious Adverse Event Reporting

SAEs occurring from the beginning of the first infusion of the investigational product up to and including 30 days after the last infusion of the investigational product will be reported to the study Sponsor or its designee within 24 hours of the investigator becoming aware of the event. SAEs occurring after 30 days following the last treatment with the investigational product, which, in the judgement of the investigator or treating physician, are *possibly, probably or*

***definitely*** related to treatment with the investigational product, will be reported to the study Sponsor or its designee within 24 hours of the investigator becoming aware of the event.

Initial SAE reports must be followed by detailed descriptions. These should include copies of hospital case records and other documents when requested. Telephone reports must be confirmed promptly by written report.

Additionally, the Investigator is responsible for submitting follow-up reports for all SAEs until the SAE has resolved or until the subject's condition stabilizes (in case of persistent impairment), or the study participant dies.

A death (including death due to progressive disease) occurring within 30 days after the last T cell infusion must be reported to the Sponsor or its designee within 24 hours of site awareness of the death whether or not it is considered treatment-related. Any death occurring greater than 30 days after the last T cell infusion must be reported to the Sponsor or its designee within 24 hours of site awareness of the death only if it is possibly, probably, or definitely related to treatment with the investigational product.

The investigator also must notify the IRB/Institutional Ethics Committee (IEC) and/or Institutional Biosafety Committee (IBC) of the occurrence of the SAE, in writing, as soon as is practicable and in accordance with local law. A copy of this notification must be provided to the study Sponsor or its designee.

#### **11.7.1 Study-specific SAE reporting**

Planned hospitalization will not be reported to the Sponsor as an SAE. Planned hospitalizations may include admission for:

- entry into the study
- elective treatment of a pre-existing condition
- routine monitoring of the subject not associated with any deterioration in condition
- monitoring following CAR T cell infusion if minor (non-serious) symptoms indicate the potential for more significant medical problems

#### **11.8 IND Safety Reporting**

This study will comply with 21 CFR 312.32, which requires that the sponsor notify the FDA and participating investigators in an IND Safety Report of potentially serious risks from clinical trials or any other source. Reports must be submitted no later than 15 calendar days after the Sponsor becomes aware of the information and determines it is reportable.

The Sponsor will submit an IND Safety Report for individual events meeting the following criteria:

- There is a reasonable probability the drug under study caused the event (ie, there is evidence to suggest a causal relationship between the drug and the AE)
- The event meets the criteria in Section 11.2 Definition of Serious Adverse Event (SAE) for a serious adverse event
- The event is unexpected (ie, it is not consistent with the risk information in the protocol or other information submitted to the FDA in the IND)

Analysis of one or more occurrences of the same event, and/or aggregate analysis of specific events, may lead the Sponsor to determine that information requires reporting via an IND Safety Report.

The period for IND safety reporting extends from the beginning of the first infusion of the investigational product up to and including 30 days after the last infusion of the investigational product.

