**Table 3-2 Serum Creatinine ULN Based on Age and Sex**

| Serum Creatinine (mg/dL) ULN |      |        |
|------------------------------|------|--------|
| Age                          | Male | Female |
| 1 to < 2 yrs                 | 0.6  | 0.6    |
| 2 to < 6 yrs                 | 0.8  | 0.8    |
| 6 to <10 yrs                 | 1    | 1      |
| 10 to < 13 yrs               | 1.2  | 1.2    |
| 13 to < 16 yrs               | 1.5  | 1.4    |

|               |     |     |
|---------------|-----|-----|
| $\geq 16$ yrs | 1.7 | 1.4 |
|---------------|-----|-----|

10. Adequate hepatic function as indicated by either of the following:
  - a. Total bilirubin < 3 times ULN for age, OR
  - b. Conjugated bilirubin < 2 mg/dL
11. Adequate respiratory function as indicated by BOTH of the following:
  - a. Oxygen saturation  $\geq 90\%$  on room air without supplemental oxygen or mechanical ventilation, AND
  - b. No dyspnea at rest
12. Adequate neurologic function as indicated by all of the following:
  - a. Signs and symptoms of neurologic deficit must be stable for  $\geq 1$  week prior to enrollment, AND
  - b.  $\leq$  two anti-epileptic agents are required to control seizure activity, AND
  - c. No clinically evident encephalopathy present
13. Virology negative within 3 months prior to enrollment, to include all of the following:
  - a. HIV antigen & antibody, AND
  - b. Hepatitis B surface antigen, AND
  - c. Hepatitis C antibody OR if antibody positive, Hepatitis C polymerase chain reaction (PCR) is negative
14. Subjects of childbearing/fathering potential must agree to use highly effective contraception (Appendix 6 – Highly Effective Contraception) from the time of enrollment through 12 months following the last T cell infusion

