## **7.19 Post-Treatment Long-Term Follow-Up data collection**

Research participants who receive engineered T cells will be required to participate in long-term follow-up (LTFU) per the guidelines set forth by the FDA's Biologic Response Modifiers Advisory Committee that apply to gene transfer studies to capture delayed adverse events related to the use of lentivirally transduced T cells.

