### **11.10 Reporting of Pregnancy**

Pregnancies in study participants or partners that occur from time of consent through 28 days following administration of investigational product or in subjects with continued persistence of CAR T cells (whichever is later) must be reported within 24 hours of site awareness of the event to the study Sponsor or its designee. Subjects who become pregnant prior to the initial administration of investigational product will be taken off study. If pregnancy in subject's partner occurs after administration of investigational product, the investigator must make every effort to follow the pregnancy of either the participant or partner through resolution of the pregnancy (delivery or termination) and report the resolution to the study sponsor or its designee. In the event of a pregnancy in the partner of a participant, the investigator should make every effort to obtain the female partner's consent for release of protected health information.

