| Correlative Sciences: PB         | CAR T cell persistence                  |                                                       | X       |         | X                 | X        | X                 | X        | X                 | X        | X                 | X        | X                 |
|                                  | Replication-competent lentivirus (RCL)  | X                                                     | X       |         | X                 |          |                   |          |                   |          |                   |          |                   |
| MRI brain & spine  |                                                     | X                                                     | X       | X       | X                 |          |                   |          |                   |          |                   |          |                   |
| Adverse events       |                                                     | Continuous                                            |         |         |                   |          |                   |          |                   |          |                   |          |                   |

 If performed for clinical indication. May be obtained from local provider or treating oncologist

 Medical events relevant to subject's disease and treatment, inclusive of infectious disease. If relevant, records pertaining to disease response and/or relapse will be collected.

 Testing at all time points must include cell count and cytology. Any additional material obtained for clinical purposes may be sent to CSL for research testing. Disease Evaluations are no longer required if progressive disease was confirmed in a prior evaluation.

 Timepoints only applicable if ongoing T cell persistence in peripheral blood at the end of protocol therapy/discontinuation visit. CAR T cell persistence testing will be discontinued after a negative result.

 MRI of the spine for subjects with previous spinal disease, positive CSF cytology, or cause for clinical concern. Disease Evaluations are no longer required if progressive disease was confirmed in a prior evaluation.

 The following are Delayed Related AEs of interest that must be reported to the Sponsor: development of a new malignancy, or neurologic, rheumatologic, autoimmune, or hematologic disorder

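### Section 11.8 closes IND safety reporting 30 days after the last infusion, which contradicts its own opening, Section 11.7 and the 15-year follow-up; a narrower mismatch affects pregnancy reports

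*Protocol*

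**What the plan says.** **IND reporting.** Section 11.8 opens by committing the study to 21 CFR 312.32, under which the Sponsor notifies the FDA and participating investigators of "potentially serious risks from clinical trials or any other source". It sets a limit of 15 calendar days from Sponsor awareness and determination, and lists three criteria for an individual report: evidence of causality, seriousness and unexpectedness. It closes with "The period for IND safety reporting extends from the beginning of the first infusion of the investigational product up to and including 30 days", counted from the final infusion.

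**Reports from site to Sponsor.** Section 11.7 covers "SAEs occurring after 30 days following the last treatment with the investigational product" if judged possibly, probably or definitely related. These go to the Sponsor within 24 hours, and no end date is given. Section 11.2 counts a secondary malignancy and a congenital anomaly as serious.

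**Long-term follow-up.** Section 7.19 gives its purpose as "to capture delayed adverse events related to the use of lentivirally transduced T cells". Section 9.1 puts its length at 15 years. Appendix 2 Table 2 states: "The following are Delayed Related AEs of interest that must be reported to the Sponsor: development of a new malignancy", and goes on to neurologic, rheumatologic, autoimmune and hematologic disorders. Table 3 repeats the rule for years 6 to 15.

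**Pregnancy.** Section 11.10 requires a report within 24 hours for "Pregnancies in study participants or partners that occur from time of consent through 28 days following administration of investigational product". It extends this to subjects in whom CAR T cells persist, taking the later of the two. Inclusion criterion 14 in Section 3.2.1 requires highly effective contraception "from the time of enrollment through 12 months following the last T cell infusion".

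**The concern.** The long-term follow-up exists to find late harm from gene-modified cells. Under Section 11.7 and the Appendix 2 tables, a late related event reaches the Sponsor. The next step is the expedited report to the FDA and participating investigators, and the last sentence of Section 11.8 places that step outside its stated period from day 31 onward. Someone applying that sentence as an operating rule could conclude that no IND Safety Report is due for exactly the events the follow-up was set up to detect, while other children and young adults are still being infused.

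The pregnancy rule raises a smaller question of the same kind. The protocol asks subjects to avoid pregnancy for a year after the last infusion, but for some of them it does not ask to be told of a pregnancy in most of that year.

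**Working it through.** The plan states no figure to reproduce. The check sets the windows side by side.

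| Provision | Section | Ends |
|---|---|---|
| IND compliance, 15-day limit, three criteria, aggregate analysis | 11.8, body | No end stated |
| IND safety reporting period | 11.8, last sentence | 30 days after last infusion |
| Related SAEs to Sponsor | 11.7 | No end stated |
| Delayed related AEs to Sponsor | 7.19, Appendix 2 Tables 2 and 3 | 15 years after last infusion |
| Pregnancy report, no detected persistence | 11.10 | 28 days after administration |
| Pregnancy report, continued persistence | 11.10 | While cells persist, if later |
| Contraception | 3.2.1, criterion 14 | 12 months after last infusion |

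**Step 1: trace one event.** Take a new malignancy in year 2 after the last infusion, judged related and unexpected.
- Serious? Yes, under 11.2.
- To the Sponsor? Yes, within 24 hours under 11.7, and also under Table 2.
- Does it meet the three criteria in 11.8? Yes, by assumption.
- Is it inside the period in the last sentence of 11.8? No.

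The event therefore qualifies under the body of 11.8 and is excluded by its last sentence. Both cannot govern.

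**Step 2: would others still be under treatment?** Section 9.1 anticipates 6 years (72 months) of accrual and up to 7 months of active treatment. For a subject treated at the start of accrual, ignoring manufacturing time, year 2 after the last infusion runs from month 7 + 12 = 19 to month 7 + 24 = 31, well before month 72. A late event in an early subject can therefore occur while others are being enrolled and infused.

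**Step 3: pregnancy window.** Section 11.10 refers to administration of the product without saying which infusion. Taking it as the last infusion gives the longest base window. For a subject without detected persistence, the uncovered part of the contraception period is 365 − 28 = 337 days. For a subject with continued persistence there is no fixed 28-day stop, and the window can exceed 12 months.

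**Step 4: how far does the persistence extension reach?** Under Table 2, footnote 4, the long-term persistence timepoints apply only if cells were found in peripheral blood at the end-of-therapy visit, and testing stops after a negative result. That visit normally falls within 14 days of the final infusion. A subject who is negative then has no further scheduled persistence test, so the extension would not be triggered later.

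**The case against.** The strongest reply is that the opening of Section 11.8 governs. It adopts the regulation, reaches risks from any source, and carries no time limit; nor do the 15-day limit, the three criteria or the aggregate-analysis clause. A reader might infer from the last sentence that nothing at all is owed to the FDA or to investigators after day 30. The section as a whole does not support that. What it contains is an internal conflict, and if the opening prevails, the last sentence is simply wrong and should go.

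A reader might also infer that detection of late harm leads to no action. That is not supported either. The investigator must notify the IRB/IEC and/or IBC of SAEs (11.7). The weekly meeting reviews follow-up information for each subject (9.11.1). The DSMB reviews toxicity about every 6 months and can be convened at any time (9.11.2). Enrollment is described at one hospital (9.1), so the investigators treating other subjects are largely in that weekly meeting. These routes stand, but none is an IND Safety Report.

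On pregnancy, it would be too strong to say that reporting stops at 28 days for everyone, because the persistence clause extends it. It would also be too strong to say that a birth defect would go unreported and unfollowed. A congenital anomaly is an SAE under 11.2, a related one is reportable under 11.7 without end date, and the sentence in 11.10 on following a partner pregnancy to resolution has no 28-day limit. It can fairly be added that contraception and reporting windows serve different purposes and need not be identical. What stands is a gap in the initial report, from day 28 to month 12, for subjects without detected persistence. Without that report, learning of an affected birth depends on later contact and a judgement of relatedness.

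It is tempting to express the gap as a share of the calendar (30 days out of 15 years). That ratio measures time, not risk or expected missed reports. The 15 years is also a maximum, since subjects leave the study on death or on joining a separate gene-therapy follow-up protocol (8.2).

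**Conclusion.** The main point holds as a contradiction in the current text. The last sentence of Section 11.8 conflicts with that section's own opening, with 11.7, and with 7.19 and Appendix 2 Tables 2 and 3. Read literally, any serious, unexpected, related event from day 31 to the end of follow-up is known to the Sponsor but outside the stated IND period. How many such events to expect cannot be derived from the protocol. The finding rests on the sentence being unqualified, not on an assumed event rate.

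The secondary point holds only in its narrow form: about 337 days without an initial pregnancy-report duty, for subjects without detected persistence, counting from the last infusion. It is a mismatch to reconcile and carries less weight than the IND sentence.

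**What to change.** In Section 11.8, delete the last sentence, or replace it so that IND Safety Reports apply to any serious, unexpected, suspected reaction the Sponsor learns of from first infusion through the end of long-term follow-up, expressly including those received under Section 11.7 and Appendix 2 Tables 2 and 3.

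In Section 11.10, reconcile the 28-day window with the 12-month period in inclusion criterion 14, state which infusion starts the count, and keep the clause that extends reporting while CAR T cells persist.

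The cost is a small text amendment and a few extra reports. Late related events already reach the Sponsor, and pregnancy can be asked about at follow-up contacts already scheduled. No treatment, visit or sample changes.

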### **11.9 On-Target, Off-Tumor Toxicities**

On-target off-tumor toxicities are toxicities attributable to the direct effect of CAR T cells on tissue (e.g. organ damage caused by CAR T cell direct targeting of organ cells) and not associated with a more global syndrome attributable to the CAR T cell (eg, CRS or pseudoprogression).

### **11.10 Reporting of Pregnancy**

Pregnancies in study participants or partners that occur from time of consent through 28 days following administration of investigational product or in subjects with continued persistence of CAR T cells (whichever is later) must be reported within 24 hours of site awareness of the event to the study Sponsor or its designee. Subjects who become pregnant prior to the initial administration of investigational product will be taken off study. If pregnancy in subject's partner occurs after administration of investigational product, the investigator must make every effort to follow the pregnancy of either the participant or partner through resolution of the pregnancy (delivery or termination) and report the resolution to the study sponsor or its designee. In the event of a pregnancy in the partner of a participant, the investigator should make every effort to obtain the female partner's consent for release of protected health information.

